## Abstract

**Background:**

Schizophrenia is a disorder associated with neurocognitive deficits that adversely affect daily functioning and impose an economic burden. Cognitive rehabilitation interventions, particularly during the early phases of illness, have been shown to improve cognition, functionality, and quality of life. The Feuerstein Instrumental Enrichment (FIE) program, based on the Mediated Learning Experience and the Structural Cognitive Modifiability theory, has been applied in various disorders, but its applicability in schizophrenia has not yet been clarified.

**Objective:**

This study aims to investigate the effects of the FIE program on the functionality of patients with first-episode schizophrenia.

**Methods:**

In total, 17 patients will be recruited for an open-label intervention consisting of twice-weekly sessions for 10 weeks. The primary outcome measure will be changes in the Goal Achievement Scale score. Maze task performance from the Measurement and Treatment Research to Improve Cognition in Schizophrenia (MATRICS) battery will serve as a secondary outcome measure. At the same time, changes in Positive and Negative Syndrome Scale scores and other MATRICS domains will be analyzed as exploratory outcomes. Assessments will be administered before and after the intervention, with a follow-up period of 6 months.

**Results:**

This trial was preregistered in The Brazilian Registry of Clinical Trials (RBR-4gzhy4s). By February 2024, 11 participants were enrolled in the training. Recruitment is expected to be completed by May 2024. Data analysis will be conducted between May and September 2024. The results are expected to be published in January 2025.

**Conclusions:**

This study may establish a protocol for the FIE program that uses mediation techniques for individuals in the early stages of schizophrenia. The results will add to the knowledge about strategies to promote cognitive skills and functional impairment in daily life.

**International Registered Report Identifier (IRRID):**

DERR1-10.2196/57031

## Introduction

### Background

Schizophrenia is a debilitating mental disorder characterized by hallucinations and disorganized thinking. It is influenced by genetic, neurological, and social factors that affect brain development and functioning [1]. Individuals often exhibit socialization difficulties and cognitive deficits [2] that are associated with low recovery rates [3-6].

Cognitive impairments, including deficits in executive functioning, processing speed, cognitive control, attention, working memory, and social cognition, are core features of schizophrenia [7-9]. Visual processing and perception impairments, including motion, color perception, and perceptual organization, are also observed and are associated with disorganization symptoms [10].

Cognitive deficits can be detected during the early stages of the illness, even up to a decade before the first episode of psychosis [2]. Despite initial improvement [11], the cognitive abilities of individuals experiencing their first episode of psychosis are similar to those of patients with chronic schizophrenia [12-14]. Furthermore, up to 90% of individuals diagnosed with schizophrenia may experience recurrence within 3 years [13]. The connection between clinical and cognitive insight, which in turn affects relapse rates, is well-established [15]. Specific cognitive skills, such as prospective memory, attention, and working memory, have been shown to impact both medication adherence [15] and overall functionality [16].

Cognitive remediation interventions in schizophrenia have been investigated and shown to improve neurocognition [17], although there is limited evidence of the generalization of trained abilities to daily life functioning [18]. On the other hand, studies have shown that cognitive remediation interventions that incorporate psychotherapy features, where therapists actively discuss behavioral and cognitive alternatives for the activities and personalize and contextualize the exercises to the real world, have the potential for higher generalization of cognitive gains to daily life [17,18].

The Feuerstein Instrumental Enrichment (FIE) program [19] is a paper-pencil set of tasks developed by Reuven Feuerstein based on 2 main principles that are, Mediated Learning Experience (MLE) and Structural Cognitive Modifiability (SCM) theory [20,21]. It has 14 tools or instruments, divided into 3 modules according to task complexity and progressive learning skills.

The FIE method is grounded in the foundational principle of altruism, with the intention of providing aid and support to individuals undergoing cognitive transformation. The mediator assumes the responsibility for making activities, tasks, and the environment comprehensible from an individual’s perspective [22]. In the learning process, the mediator has a pivotal role in establishing purposeful intentions, providing guidance, and interpreting and personalizing stimuli to improve an individual’s understanding of the world and themselves. This method fosters metacognition and the acquisition of personal knowledge [23,24].

The MLE is the basis for cognitive modification proposed by the SCM theory [24]. It emphasizes the possibility of developing new behaviors, skills, and cognitive abilities not previously presented in someone’s individual functioning [22]. This repertoire is associated with neuroplasticity and, consequently, neurophysiological changes [22].

SCM theory proposes cognitive modification using MLE [24]. MLE facilitates the acquisition of new behaviors, skills, and cognitive abilities that were not previously present in an individual’s functioning [22]. This acquisition is associated with neuroplasticity and subsequent neurophysiological changes [22]. The FIE program, a top-down paradigm, has been previously used for visual-perception organization training in patients with schizophrenia [25]. It has been associated with improvements in perceptual organization abilities and broader cognitive functions compared with computer-based bottom-up interventions such as CogPack (marker software GmbH).

Instrumental enrichment has been previously used for visual-perception organization training in patients with schizophrenia by Kurylo et al [25]. They compared 2 interventions, focused on perceptual organization, to a control intervention (a computer nonvisual-perceptual task, CogPack), of which one was a computer-based bottom-up intervention based on Gestalt principles, requesting the participant to group stimuli according to visual characteristics, like luminance, color, line orientation, and motion. The other was 2 of the 14 instruments from the FIE program, following a top-down paradigm: organization of dots and an analytic perception task. They found that both visual perception interventions were superior to the control task for the improvement of perceptual organization ability, generalizing gains to other visual cognitive tasks. Furthermore, FIE was also associated with improvements in broader cognitive functions compared with the other 2 interventions.

While FIE has the potential to improve cognitive flexibility and problem-solving through group mediation, its potential to generalize has not been explored. Therefore, this study aims to investigate the effects of peer-mediated FIE interventions on daily life functionality in patients with FES. The hypothesis is that FIE intervention will lead to improvements in daily life functionality in patients with FES.

Regardless of the cognitive visuo-perceptual improvement, FIE has great potential to improve cognitive flexibility and problem-solving through group mediation and has a high potential to generalize 2 features that were not explored by Kurylo et al [25]. In this study, we investigate the effects of peer FIE intervention on the functionality of patients with FES. Our main hypothesis is that FIE intervention improves daily life functionality in patients with FES.

### Aims and Objectives

This study aims to investigate the effects of the FIE intervention, delivered through a peer-mediator group format, on functionality in individuals with schizophrenia. Functionality will be evaluated based on individual goal achievement using the Goal Achievement Scale (GAS) [26,27]. Secondary outcomes will include changes in problem-solving and reasoning, measured through the maze task from the Measurement and Treatment Research to Improve Cognition in Schizophrenia (MATRICS) score [28]. Exploratory analysis will also investigate changes in the Positive and Negative Syndrome Scale (PANSS) scores [29] and other MATRICS domains.

## Methods

### Research Design

The proposed research design is an open-label interventional pilot study that aims to investigate the effects of the FIE program on the functionality of patients with FES based on their personal goals. The study will measure outcomes at 3 time points that are baseline (t0), after the intervention (t1), and at the 6-month follow-up (t2).

### Participants

Participants for this study will be recruited from the Early Intervention Group of the Federal University of São Paulo, as well as from other first-episode programs and public and private psychiatric offices in São Paulo. To be eligible, participants must be between 18 and 40 years old and have a diagnosis of schizophrenia according to the *Diagnostic and Statistical Manual of Mental Disorders, Fifth Edition* (*DSM-5*) criteria [30], as confirmed by the Structured Clinical Interview for DSM-5-Research Version (SCID-5 RV) Axis I disorders [31], and received treatment for psychosis while being clinically stable, according to their psychiatrist. Participants must also have an estimated IQ of 70 or higher and be able to provide informed consent. Exclusion criteria include an inability to understand or communicate in Portuguese, any organic or neurological health condition that impacts cognition, substance abuse or dependence (except nicotine), and an estimated IQ lower than 70, indicating intellectual disability. A patient flowchart is shown in Figure 1.

**Figure 1 figure1:**
[figure not shown]
Study design and patient flowchart. (1) We applied the informed consent form, IQ assessment, and Structured Clinical Interview for DSM-5-Research Version. (2) Participants who are deemed ineligible or unwilling to participate or continue in this study will be removed from the study. (3) We conducted baseline assessments using Measurement and Treatment Research to Improve Cognition in Schizophrenia (MATRICS), Positive and Negative Syndrome Scale, and Goal Achievement Scale. (4) We are awaiting a group of 2-3 eligible participants who have successfully completed the IQ and MATRICS assessments. (5) A 10-week training program with Feuerstein Instrumental Enrichment (FIE) will be conducted, with a frequency of 2 sessions per week. (6) A postintervention assessment will be conducted 1 week after the completion of the FIE program. (7) A follow-up assessment will be conducted 6 months after the completion of the FIE program. (8) The primary outcome of the study will be functionality, which will be measured using the Goal Attainment Scale scores. In addition, problem-solving and reasoning abilities will be assessed using the maze scores from the MATRICS assessment.

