### Intervention

The intervention will comprise 2 weekly sessions conducted over a period of 10 weeks. Patients will be enrolled in a pair or 3-person group and will always be accompanied by a mediator. Participation will be continuous and dependent on the patients’ interest and fulfillment of the inclusion criteria. The intervention will use 3 tasks from the FIE program-standard instrument I, namely organization of dots, orientation in space I, and analytic perception [32].

The organization of dots task involves identifying geometric images from a cloud of dots; the patient is required to draw lines to connect the dots and form the geometric image. To complete this task, it is necessary to project and create a virtual relationship between elements, focusing on the relevant aspects of the figure.

The orientation in space I task focuses on visuospatial flexibility and perception of the world, making the patient recognize and differentiate the position of objects on the paper sheet, exploring the patient’s own references regarding left, right, front, and back to identify the position of objects in relation to others. This task promotes problem definition and solving strategies, hypothetical thinking, and the creation of conditionals (ie, If… then...) and comparison strategies with peers.

The analytic perception task practices the differentiation and integration of images. In this task, there is a model image, and there are several options for possible responses. The options are a set of shapes that need to be mentally grouped to form the model image, such as a jigsaw. The patient needs to analyze the options and choose the 1 that corresponds to the model. It explores the perceptual ability to focus on specificities, splitting the whole into parts, and the ability to see the whole picture, gathering parts into 1 element.

Each session will take 1-hour and involves 3 steps [20,32]:

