### Functionality Assessments

The GAS is a type of assessment that is centered on personal goals and is commonly used in physical rehabilitation (lifestyle, type of handicap, and aspirations) but is not often used in psychiatry [26,27]. GAS was first used in mental health settings in the 1960s and has also been applied for cognitive rehabilitation [33,35].

The patient and interviewer work together to define individual goals that are specific, measurable, attainable, realistic, and timely, using the “SMART” method. These goals are based on the patient’s current lifestyle, daily routines, interests, and needs. If a patient expresses a desire for a long-term goal that cannot be achieved in a short time, the interviewer helps the patient break it down into smaller achievable goals that fit within a defined time frame. The GAS score is based on a defined goal and considers its weightage. Achievement of the defined goal is typically scored as 0, and if the achievement is better or worse than that defined, the score is either +1 or +2 or 1 or 2, respectively. The patient also rates the importance and difficulty of each goal on a 0-3 Likert scale. The final score is calculated by an algorithm that provides a baseline score, an achieved score, and the difference between the two [27].

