## Results

This trial has been preregistered in the Brazilian Registry of Clinical Trials (RBR-4gzhy4s). Recruitment started in February 2022, and by February 2024, 11 participants were enrolled in the training. Recruitment is expected to be completed by August 2024. Data analysis will be conducted between May and September 2024. The results are expected to be published in peer-reviewed journals and presented at mental health conferences after January 2025.

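### Baseline GAS, PANSS and MATRICS precede the wait for a training group, so the uncontrolled t0-t1 change includes an FIE-free period that varies between patients

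*Protocol article*

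**What the plan says.** The order of events is in the caption to Figure 1 of the protocol article:

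- Step "3) We conducted baseline assessments using Measurement and Treatment Research to Improve Cognition in Schizophrenia (MATRICS), Positive and Negative Syndrome Scale, and Goal Achievement Scale".
- Step "4) We are awaiting a group of 2-3 eligible participants who have successfully completed the IQ and MATRICS assessments".
- Step "5) A 10-week training program with Feuerstein Instrumental Enrichment (FIE) will be conducted, with a frequency of 2 sessions per week".
- Step "6) A postintervention assessment will be conducted 1 week after the completion of the FIE program".

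The Intervention section confirms the group size: "Patients will be enrolled in a pair or 3-person group and will always be accompanied by a mediator". Research Design defines three time points only (t0, t1, t2), so t0 is the single pre-treatment value.

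Under Functionality Assessments, GAS goals are agreed with the patient. Where a goal is long-term, "the interviewer helps the patient break it down into smaller achievable goals that fit within a defined time frame". The score is built from a baseline score, an achieved score and their difference.

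On accrual, the Results section says: "Recruitment started in February 2022, and by February 2024, 11 participants were enrolled in the training". Participants must be receiving treatment for psychosis and be clinically stable (Participants section). The Limitations section acknowledges that there is no control group but does not mention the wait.

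**The concern.** Patients are measured, then wait for one or two partners, and only then start FIE. The t0-t1 interval is therefore the wait plus the training period. Without a control arm or a second pre-treatment measurement, change during the wait cannot be separated from change during training. Progress on goals, the effect of continuing usual treatment, and any effect of having set goals at all would be added to the apparent FIE effect.

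GAS is the most exposed outcome, because goals are agreed with the patient at baseline and scored on what has been achieved since. The exposure is also unequal: within one group, the first patient's t0 is older than the last patient's. That adds spread to the change scores that has nothing to do with FIE.

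**Working it through.** **1. Order of events.** Baseline is step 3, the wait step 4, training step 5. The numbering is not a loose convention, because step 4 itself requires waiting members to have completed MATRICS. With 10 weeks of training and t1 one week later:

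t0-t1 = wait + 10 + 1 = wait + 11 weeks.

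**2. The plan's own figure.** The article gives no figure for the wait. The only related figure is the power of 0.62 for a matched-pairs t test on GAS (N = 17, d = 0.5, Power and Sample Size section). With df = 16 and noncentrality 0.5 × √17 = 2.06, the noncentral t distribution gives 0.629 at one-sided 0.05 and 0.491 at two-sided 0.05. The stated value matches the one-sided test. Alpha and sidedness are not stated, so step 5 shows both.

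**3. Wait implied by accrual (assumption: evenly spaced arrivals into one queue).**

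- Gap between arrivals: m = 24/11 = 2.18 months.
- Pair: the first member waits 2.18 and the second 0. Mean 2.18/2 = 1.09 months.
- Trio: the members wait 4.36, 2.18 and 0. Mean 6.54/3 = 2.18 months.

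As a share of t0-t1, at 4.345 weeks per month:

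| Patient | Wait (weeks) | t0-t1 (weeks) | Share before session 1 |
|---|---|---|---|
| Mean, pairs | 4.7 | 15.7 | 30% |
| Mean, trios | 9.5 | 20.5 | 46% |
| First of a pair | 9.5 | 20.5 | 46% |
| First of a trio | 18.9 | 29.9 | 63% |
| Last of any group | about 0 | 11 | about 0% |

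**4. Range under faster accrual.** The remaining 17 − 11 = 6 patients are expected by May 2024 (Abstract) or August 2024 (Results). From February 2024 that is 6/3 = 2.0 or 6/6 = 1.0 per month.

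- At 1.0 per month: mean wait 0.5 month (pairs) or 1.0 month (trios); first member 1.0 or 2.0 months.
- At 2.0 per month: mean wait 0.25 or 0.5 month; first member 0.5 or 1.0 month.

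So the mean wait ranges from about 0.25 to 2.2 months, depending on accrual and group size.

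**5. What a change during the wait would do (illustration; the drift is assumed, not documented).** Suppose FIE has no effect and the only change is a drift during the wait, in SD units of the change score. The probability of a significant result in favour of FIE at N = 17 is then:

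| Assumed drift | One-sided 0.05 | Two-sided 0.05, favourable direction |
|---|---|---|
| 0 | 5% | 2.5% |
| 0.2 | 20% | 12% |
| 0.3 | 32% | 21% |

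The Analysis section names other tests than the t test. The bias does not depend on that choice, because any comparison of t0 with t1 carries the same interval.

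**The case against.** Several points on the other side have force.

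- **Length of the wait.** The article never gives it. Accrual is a proxy: the Results section counts patients enrolled in training, not the dates of their baseline visits. There are several recruitment sources, and two groups may run in parallel. A reader might infer that every patient waits for months, or that half or more of t0-t1 falls before any session. The documents do not support either. Even with evenly spread arrivals, only the first member of a trio passes half (63%), and because pairs are allowed nothing obliges a patient with one partner to wait for another.
- **Untreated waiting.** A reader might also infer that patients are untreated while they wait. The Participants section says otherwise: they are under treatment for psychosis. The wait is free of FIE, not of treatment.
- **The GAS clock.** Goals that "smaller achievable goals that fit within a defined time frame" need not be timed from the baseline visit; a frame tied to the end of training would fit the text equally well. Step 4 names IQ and MATRICS as complete, not GAS. But step 3 lists GAS with the other baseline measures, and the achieved score is still compared with a baseline set before the wait.
- **Missing detail.** A journal article may leave visit windows to the full protocol, so the lack of a stated maximum wait is not itself the point. The point is the order that the article does state.
- **Already disclosed.** The absence of a control group is named as the major limitation, and moving the baseline would not remove confounding during training. That stands. The wait is nevertheless a separate and avoidable part of the interval, and it is not disclosed.

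**Conclusion.** The point holds as one about the order of assessments. As described, the primary t0-t1 change includes an FIE-free wait on usual treatment that differs between patients, and nothing in the design separates it from the FIE effect. The direction and size of any resulting bias are unknown, because neither the waits nor the progress made during them are documented.

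Under evenly spread arrivals at the reported accrual, the wait would average about 1.1 to 2.2 months, or 30% to 46% of t0-t1; clustered or faster recruitment would reduce it to weeks. This is a cheap improvement to an uncontrolled pilot. It does not invalidate the study, and the correction does not replace a control group.

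**What to change.** **Patients not yet assessed (at most 17 − 11 = 6).** Keep consent, SCID and IQ screening first. Form the group, then carry out GAS goal setting, PANSS and MATRICS within a short fixed window before session 1 (for example 2 weeks), and define that as t0. MATRICS is not an eligibility criterion in the Participants section, so it need not precede group formation. The assessments are moved, not repeated, so there is no added MATRICS practice effect.

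**Patients already enrolled.** Report the baseline-to-session-1 interval for each patient and show GAS change against it as a descriptive sensitivity analysis. With so few patients, a subset defined by a cut-off chosen afterwards would be imprecise and should not carry a conclusion.

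**Text.** Correct the order in the Figure 1 caption and name the wait as a limitation beside the missing control group.

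**Cost.** Two or three baseline visits per group must be scheduled close together. Baseline timing will also differ between earlier and later patients, which the report should state. No assessment is added.

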### Intervention

The intervention will comprise 2 weekly sessions conducted over a period of 10 weeks. Patients will be enrolled in a pair or 3-person group and will always be accompanied by a mediator. Participation will be continuous and dependent on the patients’ interest and fulfillment of the inclusion criteria. The intervention will use 3 tasks from the FIE program-standard instrument I, namely organization of dots, orientation in space I, and analytic perception [32].

The organization of dots task involves identifying geometric images from a cloud of dots; the patient is required to draw lines to connect the dots and form the geometric image. To complete this task, it is necessary to project and create a virtual relationship between elements, focusing on the relevant aspects of the figure.

The orientation in space I task focuses on visuospatial flexibility and perception of the world, making the patient recognize and differentiate the position of objects on the paper sheet, exploring the patient’s own references regarding left, right, front, and back to identify the position of objects in relation to others. This task promotes problem definition and solving strategies, hypothetical thinking, and the creation of conditionals (ie, If… then...) and comparison strategies with peers.

The analytic perception task practices the differentiation and integration of images. In this task, there is a model image, and there are several options for possible responses. The options are a set of shapes that need to be mentally grouped to form the model image, such as a jigsaw. The patient needs to analyze the options and choose the 1 that corresponds to the model. It explores the perceptual ability to focus on specificities, splitting the whole into parts, and the ability to see the whole picture, gathering parts into 1 element.

Each session will take 1-hour and involves 3 steps [20,32]:

Introduction: The mediator highlights the task’s novelty and complexity, guiding patients toward the solution to the problem.The task itself, where patients will work with the instrument and mediator, will observe their behavior, strategies, and reactions, mediating the process and acting as a bridge between the instrument and patients. The mediator will also provide feedback and correct answers and prevent frustration, among other things.Conclusion: Patients will practice the transfer of knowledge acquired during the session to daily life, discussing the exercise’s realization and the processes used during the intervention.

In this pilot study, one of the coauthors ([name]) will be enrolled as a mediator, applying the intervention to all participants in all groups. Furthermore, 2 parallel groups can be run over time. The mediator graduated in the educational field and has been certified by the Feuerstein Institute since 2009. She has more than 10 years of experience as an FEI practitioner and is currently an authorized FEI trainer in Brazil.

